**DATA SOURCES**

1. Victorian Perinatal Data Collection
   1. Approximately 1,000,000 Victorian births between 2005-2018
   2. Routinely-collected data from the electronic Birthing Outcome System (BOS).
2. Major IVF providers in Victoria
   1. Cycle data from all pregnancies that resulted in a birth from each of the following IVF providers 2005-2018 (approximately **30,000 cycles):**
      1. Melbourne IVF
      2. Monash IVF
      3. City Fertility Centre
3. Australian Early Developmental Census
   1. Performed *every three years* across Australia. These data are collected by prep school teachers who conduct an observational assessment of every child in their first year of full-time primary school.
   2. Birth data to be linked with corresponding AEDC data from 2009 (unlikely to link with births in our study cohort), **2012, 2015, 2018.**
   3. **Five domains of assessment:**
      1. Physical health and wellbeing – looks at absence from school due to illness, independence with toileting, coordination, fine motor skills and physical ability to climb stairs, and other aspects.
      2. Social competence – assesses ability to get along with peers, respect for adults and others, curiosity about the world and eagerness to play and learn, willingness to help other children who are hurt or having difficulty with an activity and problem-solving day-to-day tasks.
      3. Emotional maturity – aims to identify impulsive or bullying behaviour, as well as the child’s ability to make decisions, be patient and attentive, share and wait their turn in games.
      4. Language and cognitive skills – assesses ability to use English effectively; listen and follow instructions in addition to more in-depth assessments of reading, writing and numeracy.
      5. Communication skills and general knowledge – looks at the child’s ability to tell a story, participate in imaginative play, communicate their own needs to their peers and to adults and assesses their knowledge about the world (eg. the seasons, types of fruit, different animals etc).
   4. From the teacher’s assessment, an individual score is calculated for each child. Outcome measures include *both* a **score** (out of 10) and a **centile** for each domain for every child. Centile scores are used to define:
      1. *developmentally “vulnerable” = <10^th^ centile (in any domain)*
      2. *developmentally “at risk” = 10-25^th^ centile (in any domain)*

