      11. BMI
      12. Other potential confounders:
          1. Parents overseas born
          2. Occupation of both parents
          3. Second parent level of education
          4. Parity

The list of covariates to be included in the propensity score model will be finalised after consideration of potential open backdoor causal paths and conditioning effects of collider nodes. The list above will be used as start. Distinction will be made between the standard epidemiological definition of a confounder and the causal pathway definition.

**Causal pathway and confounding** *(excerpt from Causal Inference , What if. M Hernan & J Robins p85:* [*https://www.hsph.harvard.edu/miguel-hernan/causal-*](https://www.hsph.harvard.edu/miguel-hernan/causal-) *inference-book/*)

“..the bias has the same structure: it is due to the presence of a cause (known covariate L or unknown covariare U) that is shared by the treatment A and the outcome Y, which results in an open backdoor path between A and Y. We refer to the bias caused by shared causes of treatment and outcome as confounding,…”

**These potential confounders (PS_covariates) will then be used in the construction of a propensity score model for exposure assignment (vide infra).**

1. Handling of missing data using Multiple Imputation

a. Consideration of missing data will be confined to all the covariates identified for the construction of a (propensity score) model of the exposure status. When imputing these missing covariate values the imputation model will include include: the outcome; all covariates identified for inclusion in the propensity score model with any transformations and interaction terms where appropriate; as well as additional auxillary covariates* from the BOS database/NAPLAN/AEDC databases. *These co-variates will be selected once the data are available for review.

b. Multiple imputation will be performed using either Multiple Imputation by Chained Equations (MICE) and/or Missing Covariate Indicator Method (MCIM) and the imputed datsets will then be used for propensity score construction. Subjects with missingness greater than 50% of PS_covariates will be excluded from analysis, this proportion will be assessed and if substantial, may result in changes to the PS_covariate list used for ongoing analysis.

c Diagnostics will then be performed to assess the quality of the imputed datasets.

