d. For each of these imputed datasets Inverse Probability Weights (IPW, vide infra) will be calculated and used in weighted regression analyses. For each outcome metric, average point estimates and standard errors (95% CI) appropriately adjusted, given the imputation framework, will be obtained. The number of imputed datasets will be set at a minimum of 20 with the number increased to equal to the highest percentage of missingness in the raw PS_covariate list (ceiling of 50% by design). Details of imputation and assessment of adequacy will be formally presented.

1. Development of Inverse Probability Weights.

a) For each imputed dataset, logistic regression with robust standard errors will be performed for the binary exposure against all the PS_covariates. Inverse probability weights will be calculated for each individual given their exposure and these will be used to weight the adjusted regression model.

b) For each imputed dataset the distribution of IPW by exposure status will be examined to ensure: (i) that there is common support (overlap) of the distributions adequacy of adjustment; and (ii) that the weighting was effective in equalizing the covariate distributions in the ‘pseudopopulation’. This will be performed using standardized difference (StD) constructed from the imputed mean minus the raw data mean for all PS_covariate, with an StD of less than 10% being considered adequate. Forrest plots comparing unadjusted and adjusted covariate distributions will also be performed.

1. Regression modelling
   1. All causal regression modelling wil be performed within the multiple imputation frame-work using the IPW propensity score-based weights.
   2. The outcome metric is considered to be absolute risk difference between IVF exposure groups. This will be performed using either generalized linear modelling with Poisson link to directly generate Relative Risks or via logistic regression modelling.
   3. Software: analysis will be performed using Stata v16 (StataCorp. 2019. *Stata Statistical Software: Release 16*. College Station, TX: StataCorp LLC. Causal inference will be performed using teffects commands (Treatment-effects estimation for observational data - see TE -teffects) run within within Stata’s multiple imputation suite.

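### The covariate-balance criterion (standardized difference under 10%) compares imputed with raw data, not the weighted exposure groups, so it cannot show whether weighting balanced IVF and natural conception

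*SAP*

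**What the plan says.** In the SAP, Part One, under Development of Inverse Probability Weights, item a) fits a logistic model for exposure on all the propensity-score covariates. It then states that "Inverse probability weights will be calculated for each individual given their exposure". Item b) sets two purposes for the diagnostics in each imputed dataset:

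- Common support: "the distribution of IPW by exposure status will be examined to ensure: (i) that there is common support (overlap").
- Balance: to ensure "that the weighting was effective in equalizing the covariate distributions in the ‘pseudopopulation".

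The next sentence says how this is to be done: by a "standardized difference (StD) constructed from the imputed mean minus the raw data mean for all PS_covariate". The acceptance limit attached to that statistic reads "with an StD of less than 10% being considered adequate". The item closes with a display: "Forrest plots comparing unadjusted and adjusted covariate distributions will also be performed".

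Imputation quality is dealt with separately, in item c of the multiple-imputation step: "Diagnostics will then be performed to assess the quality of the imputed datasets". Part Two takes over steps 1 to 3 of Part One unchanged, and Part Three uses the same methodology.

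**The concern.** The stated purpose of the balance check is right, but the statistic chosen does not measure it. Balance after weighting is a contrast between exposed and unexposed children in the weighted data. An imputed mean minus a raw mean describes how far imputation moved a covariate's average. It has no exposure contrast and no weight in it.

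This matters because the primary analysis in every part is a total effect adjusted for confounders through these weights. The 10% limit is the only numerical criterion in the plan for whether that adjustment worked. A pre-specified limit that does not respond to the weights gives no assurance about the main assumption the analysts can check.

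A secondary problem lies in the overlap check. Common support is a property of the propensity score. The plan looks for it in the weights, which are a different function of the score in each exposure group.

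**Working it through.** The SAP derives no figure here; the 10% is a criterion. The main result follows from the definition, and the numbers only illustrate it.

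**Inputs from the SAP.** Data Sources gives "Approximately 1,000,000 Victorian births between 2005-2018" and about 30,000 IVF cycles that ended in a birth, so prevalence is about 30,000 / 1,000,000 = 3%. Background gives 5% for Australian births. The largest missingness allowed for in the imputation step is 50%.

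**Assumed inputs, not in the SAP.** One normal covariate with a raw IVF-v-natural-conception difference d of 0.5, 0.8 or 1.0 SD. Missingness of 5%, 20% or 50%, either completely at random or half as frequent in the exposed. One stochastic imputation within exposure group. The SAP gives no denominator for its statistic, so the raw SD was used.

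**1. Balance statistic, by definition.**
- SAP: StD = (mean of imputed data − mean of raw data) / SD.
- What the purpose needs: StD = (weighted mean in exposed − weighted mean in unexposed) / pooled unweighted SD.

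No weight appears in the first expression, so changing or removing the weights leaves it unchanged. If nothing is missing, imputed and raw data are the same and it equals 0.

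**2. Balance statistic, simulated** (N = 1,000,000, prevalence 3% and 5%).
- SAP statistic: at most 2.2% in absolute value in every scenario. The largest value came at 5% prevalence, d = 1.0 and 50% missingness dependent on exposure.
- Hand check of that case: the exposed share among observed records is 0.05 × 0.75 / (0.05 × 0.75 + 0.95 × 0.50) = 0.0375 / 0.5125 = 0.0732. The raw mean is therefore 0.0732 and the imputed mean 0.05. The difference is −0.0232 and the SD about 1.033, giving −2.2%.
- Weighted between-group difference, correct weights: at most 1.5%.
- Weighted between-group difference, weights omitting the covariate: about 50%, 80% and 100%. These simply return the assumed d, because such weights do nothing for the covariate.

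The SAP statistic is identical under both sets of weights. The between-group statistic separates them clearly at 10%.

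**3. Reading 'imputed' as a slip for 'weighted'.** A weighted-minus-raw mean shows how far the weights moved an average, not whether the groups now agree. With all weights equal to 1 it is 0, a pass with no adjustment. Taken within the IVF group at 3% prevalence and d = 0.8, correct weights move the mean from 0.8 to the population mean 0.03 × 0.8 = 0.024. That shift of about 78% would fail precisely because the weighting worked.

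**4. Overlap of the weights.** Exposed weights are 1/p and unexposed weights 1/(1 − p). If every p is below 0.5, the first all exceed 2 and the second all lie below 2.
- No confounding, so perfect support: at 3%, 1/0.03 = 33.3 against 1/0.97 = 1.03; at 5%, 1/0.05 = 20 against 1/0.95 = 1.05.
- Simulated at 3%, d = 0.8: weights, 1st to 99th percentile, 4.6 to 153 (exposed) against 1.00 to 1.14 (unexposed). Propensity scores, 0.0065 to 0.217 against 0.0035 to 0.127, overlap well.

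**The case against.** - **The aim is correct and there is another check.** The purpose is properly stated, and plots of unadjusted against adjusted covariates are planned. This stands. A reader might infer that failed adjustment would necessarily be declared adequate. The SAP does not support that, since the plots could reveal residual imbalance. They have no acceptance rule, however, so the stated limit would still be met.
- **It may be a drafting slip.** Imputation diagnostics are planned elsewhere, which makes a slip plausible, though the text does not say so. The substitution of 'weighted' for 'imputed' does not repair the criterion.
- **The overlap check errs the other way.** A reader might infer that both diagnostics would let failed adjustment through. For IVF against natural conception, the weights barely overlap even when support is good, so the check is a false alarm or uninformative. The SAP sets no pass/fail rule for overlap, and looking at the weights is still useful for finding extreme values.
- **The rare-exposure argument does not carry over to ICSI against conventional IVF.** This stands. The SAP gives no ICSI share. With an assumed log-odds slope of 0.5 per SD, about 75%, 98%, 76% and 11% of exposed weights fall inside the unexposed 1st-to-99th percentile range at shares of 40%, 50%, 60% and 70%. Overlapping weights do not prove support either: p = 0.95 in the exposed and p = 0.05 in the unexposed both give a weight of 1/0.95 = 1.05.
- **It is a diagnostic, not the estimator.** The effect estimates do not depend on it, and the SAP names no action triggered by the result. This limits the consequence to missing assurance, but assurance is the reason for the criterion.

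**Conclusion.** The balance statistic is wrong as written. The 10% limit cannot tell whether weighting balanced the exposure groups. This rests on the definition alone and needs no assumption about covariates, missingness or prevalence. The statistic could exceed 10% if imputation moved a mean strongly, but that would be information about imputation and not about balance.

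The contrast of at most 2.2% with 50% to 100% rests on the assumed covariate differences, normality and missingness patterns. A reader might take the larger figures as the bias to expect here. They come from deliberately leaving the covariate out of the weights, whereas the SAP fits exposure on all its propensity-score covariates. With correct weights the simulated imbalance was at most 1.5%.

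The overlap point is secondary. At the SAP's prevalence of roughly 3% to 5%, the weights are the wrong quantity on which to judge common support.

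**What to change.** Reword item b) of Development of Inverse Probability Weights:

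- In each imputed dataset, define the standardized difference as the weighted exposed mean minus the weighted unexposed mean, divided by the pooled unweighted SD. Use the corresponding difference in proportions for categorical covariates.
- Report it before and after weighting, and apply the 10% limit to the after-weighting value.
- Keep the imputed-v-raw comparison only among the imputation diagnostics.
- Judge common support on the propensity score, or its logit, by exposure group. Inspect the weights separately for extreme values.

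Parts Two and Three inherit the change through their references to Part One. The cost is a few sentences of SAP text and standard software output, with no new data and no change to the estimand or the estimator.

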**PART TWO – NAPLAN**

**Causal research question:** What are the NAPLAN-defined outcomes for children conceived via IVF vs those conceived naturally?

**Exposure:** IVF conception.

**Primary outcome:** Z score to be generated from our cohort using published mean and SD for national-scaled scores.

- Means and SD for each child will be scaled to the national score for the particular year that the child was assessed. The scaled score provided is overall, thus it is expected that children in Grade 3 will have lower average scores than those in Grade 5.

**Secondary outcomes:** Above or below minimum standard for each of the four domains (binary).

**Inclusion criteria:** Children born during the study time period.

**Exclusion criteria:** Multiple pregnancies, known congential anomaly.

**Causal Inference methodology**

The analysis steps 1, 2 and 3 will be identical for that detailed above for Part One (AEDC outcome) and are not repeated here.

**Regression modelling**

- NAPLAN outcome is a continuous z-score.
- Given the cohort size it is very likely that differences in outcome between exposure groups will be highly statistically significant. The *magnitude of outcome difference* that constitutes a clinically meaningful difference is approximated by an effect size of SD 0.1, 0.2 and 0.4 – considered as mild, moderately and extremely clinically significant, respectively.
- Regression will be performed using inverse probability weighted linear regression modelling with continuous z-score as the outcome and IVF as the exposure.
- Post-analysis outcome difference will be translated and presented in a variety of effect size metrics:
  - Grattan institute - year level equivalent (EYL) of scaled score
    - Worked example: The national mean for **reading** in **2019** was 432 ELY = 3, SD was 86 so an effect size of SD of 0.1 = 423, 0.2 = 414.8 and 0.4 = 397.6 a EYL score of 2.81, 2.65 and 2.30 translating to **2**, **4** and **8** months of schooling.
      - Goss, P., and Chisholm, C., 2016, Widening gaps: what NAPLAN tells us about student progress. Technical Report, Grattan Institute

*Again, the* ***primary analysis*** *will focus on the* ***total effect*** *of IVF conception adjusted for common cause confounders. Part 4 outlines the proposed mediation analysis where* ***direct*** *and* ***indirect*** *(mediated) pathways (eg via prematurity) may be further investigated.*

**PART THREE – ICSI ANALYSIS**

ICSI forms an important and growing proportion of IVF technique. Outcomes amongst this sub-population will be explored separately and subsequent to the analyses in Part One and Two.

**Causal research question:** What is the causal effect of conception via ICSI compared to non-ICSI (conventional) IVF compared to natural conception on AEDC and NAPLAN outcomes for children?

**Exposure**: IVF with ICSI

**Primary outcome: *AEDC*** A score of <10^th^ centile in “2 or more” domains (Binary yes/no). ***NAPLAN***: Z score to be generated from our cohort using published mean and SD for national-scaled scores.

**Secondary outcomes:** ***AEDC*** A score in the lowest decile in each domain: 1) physical health and wellbeing, 2) social competence, 3) emotional maturity, 4) language and cognitive skills, and 5) communication skills and general knowledge. ***NAPLAN:*** Above or below minimum standard for each of the four domains (binary).

**Inclusion criteria:** Children born in the study time period.

**Exclusion criteria:** Multiple pregnancies, known congential anomaly.

*If there* ***ARE*** *differences in developmental and educational outcomes between ICSI and conventional IVF cohorts, we propose that this will be considered and reported as a primary finding since we have stated this sequential planned analysis a priori.*

The same methodology of causal inference, detailed in Part One and Two, will be employed for this analysis.

*Again, this analysis will focus on the* ***total effect*** *of ICSI conception adjusted for common cause confounders.*

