**CAUSAL RESEARCH QUESTION**

***What are the causal effects of Invitro Ferilization (IVF) v Natural Conception (NC) and IVF with Intracytoplasmic Sperm Injection (ICSI) v conventional IVF on the school-age developmental and educational outcomes for children?***

P – All Mothers (and their babies) who gave birth in Victoria during the period 2005-2018

*Note: we intend to consider mothers, fathers and children part of the target population even if we know that they do not have outcomes data available (e.g. AEDC)*

I – Conception via (i) any IVF; (ii) IVF with ICSI.

C – Conception via (i) natural conception (excluding ovulation induction (OI) and intra-uterine insemination (IUI)); (ii) conventional IVF.

O – Developmental and educational outcomes – AEDC and NAPLAN (Grade 3) scores.

T – The nominal age at which children are measured for AEDC (foundation school year: 4-6 years of age) and NAPLAN (school year level 3: 7-9years of age) are typically measured.

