**NULL HYPOTHESIS**

**The population distribution of school-aged developmental and educational outcomes for children conceived via conventional IVF or ICSI are the same as those of children born after natural conception.**

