      3. *developmentally “on track” = > 25^th^ centile (in any domain)*
4. National Program for Numeracy and Literacy Assessment (NAPLAN) – Victorian Data
   1. Annual school-based assessment
   2. Performed in school years 3, 5, 7, 9
   3. Four domains of assessment, each with a scaled **score** out of 1000, a “band” **category** (1-10 & 1-6 for grade 3) and a dichotomous **“**above or below” **minimum standard**.
      - *Reading*
      - *Writing*
      - *Language conventions (spelling, grammar and punctuation)*
      - *Numeracy*
      - *Overall score – overall academic ability (if data available)*

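### The SAP makes ICSI v conventional IVF a primary finding if differences are seen, without fixing the deciding outcomes, a threshold or the status of a null result

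*SAP*

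**What the plan says.** The SAP's overall causal research question has two parts. The second asks, without any condition, for the effect of "IVF with Intracytoplasmic Sperm Injection (ICSI) v conventional IVF on the school-age developmental and educational outcomes for children".

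The null hypothesis section is narrower. It states that outcome distributions after conventional IVF or ICSI "are the same as those of children born after natural conception". It does not write out a null for ICSI against conventional IVF.

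Part Three introduces the contrast in exploratory terms: "Outcomes amongst this sub-population will be explored separately and subsequent to the analyses in Part One and Two". It then labels two outcomes primary. One is the binary AEDC outcome (below the 10th centile in at least two domains). The other is a NAPLAN outcome given only as "Z score to be generated from our cohort using published mean and SD for national-scaled scores", in the same terms as Part Two. Nine outcomes are labelled secondary: five AEDC domains and four NAPLAN minimum-standard indicators.

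The reporting rule follows. Its trigger is the presence (the SAP emphasises the verb) of "differences in developmental and educational outcomes between ICSI and conventional IVF cohorts". No outcome, size or direction of difference is named in that condition. For the case where it is met, the rule reads: "we propose that this will be considered and reported as a primary finding since we have stated this sequential planned analysis a priori".

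**The concern.** The rule lets the data decide whether the contrast counts as a primary finding. Specifying an analysis in advance protects against choosing that analysis after seeing the results. It does not protect against choosing the finding's rank after seeing them, and the rank is what this sentence leaves to the result. A sequential procedure would need a gate, an error level and a named endpoint, and Part Three supplies none.

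The trigger is also loose. It speaks of developmental and educational outcomes in general, so on its literal wording a difference on any listed outcome could qualify. Even the primary NAPLAN outcome is not pinned down. The data sources section lists four domains and an overall score, the latter described as "overall academic ability (if data available"), and neither Part Two nor Part Three says which z-score is meant.

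The SAP's background section motivates the study by inconsistent evidence on the risks of ICSI. If a chance difference on one of several outcomes can be presented as a primary finding, the study could add to that inconsistency.

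**Working it through.** **Step 1: set the statements side by side.**

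- Causal research question: ICSI v conventional IVF is asked unconditionally.
- Null hypothesis: only comparisons with natural conception are written out.
- Part Three, opening: the contrast is explored after Parts One and Two, with no gate on their results.
- Part Three, reporting rule: primary if differences exist; nothing said if they do not.

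The first and last do not fit together. A question posed unconditionally should have a status that does not depend on its answer.

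**Step 2: count the outcomes that could trigger the rule.**

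- Two labelled primary outcomes, taking the z-score as a single score: 1 + 1 = 2.
- The AEDC primary plus a z-score for each of four NAPLAN domains: 1 + 4 = 5.
- Two primary outcomes plus all secondary outcomes: 2 + 5 + 4 = 11.

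**Step 3: error rate when there is no true difference.** The SAP gives no alpha, power or error rate, so there is no figure of its own to reproduce. It plans 95% confidence intervals (Part One, multiple imputation steps), so I assume two-sided 0.05 per outcome.

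For k independent tests, the chance of at least one spurious difference is 1 − 0.95^k:

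- k = 2: 1 − 0.95^2 = 9.75%
- k = 5: 1 − 0.95^5 = 22.6%
- k = 11: 1 − 0.95^11 = 43.1%

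The outcomes are correlated by construction: the AEDC domain results build the AEDC composite, and minimum standard dichotomises the NAPLAN domain results. The SAP gives no correlations. I therefore simulated 400,000 sets of equally correlated normal statistics, each √ρ·Z₀ + √(1−ρ)·Zᵢ, and counted any |z| > 1.96:

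| Tests | ρ = 0 (formula) | ρ = 0.5 | ρ = 0.9 |
|---|---|---|---|
| 2 | 9.75% | 9.1% | 7.0% |
| 5 | 22.6% | 18.3% | 10.1% |
| 11 | 43.1% | 30.3% | 13.1% |

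**Step 4: split by direction.** The rule names no direction. For spurious differences against ICSI only, the per-test rate is 0.025 and the independent formula is 1 − 0.975^k. This gives 4.9% (k = 2), 11.9% (k = 5) and 24.3% (k = 11). At ρ = 0.9 the simulation gives 3.5%, 5.1% and 6.6%. The nominal one-direction rate is 2.5%.

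**Step 5: effect of the fix.** With two deciding outcomes and 0.05 split equally (0.025 each), the chance of at least one false positive under independence is 1 − 0.975^2 = 4.94%. Holm makes its first rejection at the same 0.025 level, so it gives the same figure when neither outcome truly differs.

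**The case against.** The best defence is that the contrast, its outcomes and its place in the sequence are all specified in advance. Part Three has its own research question and its own primary outcome line, neither of them conditional. The sentence may be meant only to justify giving a later, planned analysis due prominence. The SAP also works with estimates and intervals rather than tests. Part Two turns from significance to magnitude, with benchmarks of 0.1, 0.2 and 0.4 SD, and Part Three adopts the methods of Parts One and Two.

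Much of this is fair, and it limits the point in four ways.

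- A reader might infer that a null ICSI result would be demoted or left unreported. The SAP does not say so; it is silent. The emphasised verb and the exploratory introduction make that reading natural, but it remains an inference.
- A reader might infer that the rule is tilted against ICSI. It has no direction, and about half of the spurious differences would favour ICSI.
- A reader might say that the contrast has no hypothesis at all. If both techniques give the same distribution as natural conception, they give the same distribution as each other, so a null can be derived from the joint statement. It is just not written.
- A reader might take the largest error rates as the plan's error rate. They require outcomes labelled secondary to be promoted, which the wording permits but does not state, and independence between outcomes that clearly overlap.

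The defence does not remove the conditional status itself. The magnitude benchmarks cover only the NAPLAN z-score and are not tied to the reporting rule, so they do not define what counts as a difference.

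**Conclusion.** The defect stands in a limited form. Part Three ties primary status to the contrast's own result, does not confine the trigger to its two labelled primary outcomes or to any threshold, and assigns no status to a null result. That is at odds with the unconditional research question.

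Under the assumptions above (two-sided 0.05 per outcome, no true difference, correlation from 0.9 down to 0), the chance of a spurious difference in either direction is about 7–10% on the narrowest reading. It is 10–23% if the z-score means four domain scores, and 13–43% if secondary outcomes can also trigger promotion. Every case exceeds 5%, but the size depends on an alpha and correlations that the SAP does not give.

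This should be fixed before the results are seen. It is not more serious than that: the flaw concerns labelling and reporting, and no point estimate or confidence interval changes because of it.

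**What to change.** 1. In Part Three, state that ICSI v conventional IVF is a primary comparison whatever its result, in place of the conditional sentence.
2. In the null hypothesis section, add an explicit null for this contrast.
3. Decide it on two outcomes only: the AEDC primary outcome and one named NAPLAN z-score, the same one as in Part Two.
4. State a multiplicity rule across the two. Holm is one acceptable choice, not the only one.
5. Label all other domain-level and minimum-standard results secondary, and say that they cannot alter the status of the contrast.
6. Commit to reporting the estimate and confidence interval with equal prominence if the result is null.

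The cost is a few sentences of SAP wording and a slightly stricter threshold for the two deciding outcomes. No data or modelling work changes.
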